#### *Additional tobacco measures*

For participants reporting having smoked during the follow-up period, we assess amount smoked per day, and the first two consecutive days smoked postdischarge, to calculate relapse curves by group assignment. We also collect baseline and follow-up information about other tobacco use, including cigars, pipes, bidis, hookahs, and smokeless tobacco to control for substitution. We ask about other household smokers and indoor smoking rules.

#### *Intervention dose*

We collect inpatient and outpatient smoking cessation counseling and medications provided and used by study participants from the initial inpatient consult through 12-month follow-up. Measures collected are used to assess treatment fidelity and to assess an intervention dose response on the primary outcome. Inpatient treatment measures include: TTS counseling time and content checks; medication dispenses; quit materials provided; and inpatient referrals to outpatient services (counseling programs and medication orders). These data are collected from TTS and EMR data sources. Outpatient treatment measures include: counseling program enrollment and participation, such as telephone quitlines, in-person individual and group programs, and web-based programs; FDA-approved prescription and over-the-counter medications such as buproprion, varenecline, and nicotine patches, gum, lozenges, and sprays. Medications provided and used, including combination therapy, will be assessed from EMR records and participant self-report.

#### *Intervention resource costs*

We collect tobacco cessation intervention delivery costs for study participants from the initial inpatient consult through 12-month follow-up. Cost data are obtained to support analyses from participant, health system/insurer, and societal perspectives assuming an opportunity cost approach to resource valuation. Source of payment for each expense will be used to assign costs. Intervention costs we use in the study include: TTS inpatient prescreening time; TTS patient contact time; inpatient medication dispenses; outpatient cessation counseling and medication costs; printed quit materials; IVR follow-up costs; patient travel expenditures for cessation treatment; and patient lost time from work for treatment and hourly earnings. Health system costs we use include: TTS and other staff training time; program management time; new materials development and supplies; and internal feedback reporting.

#### *Health-care utilization and expenditures*

We collect health-care utilization data beginning with the initial hospitalization through 12-month follow-up. Data include: encounters by type (primary care, emergency department, urgent care, hospital admissions); length of hospital stay (initial and subsequent hospitalizations); discharge diagnoses (ICD-9); procedures (CPT-4); pharmacy dispenses and NDC codes; diagnostic-related groups; and medical records data for health-care expenditures (actual costs based on relative-value units and paid claims; retail costs for medications) by source of payment. Data are used to assess differences in utilization and expenditures by treatment group.

#### *Health-related quality of life*

We obtain patient responses from the EuroQual (EQ5D-5L) [29-31] at baseline and six- and twelve-month follow-up for assessing changes in health-related quality of life for AR + IVR versus UC participants during the study period. Responses are combined with remaining life expectancy data for current and former smokers [32] to estimate differences in expected quality-adjusted life years saved by treatment group.

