#### *Other patient information*

Age, sex, ethnicity, race, height, weight, marital status, educational attainment, annual income, insurance coverage, time after waking before first cigarette, confidence for successful quitting, Patient-Health Questionaire-2 depression screen, and the Audit-C alcohol screen, are collected at baseline for primary and secondary outcome analyses. Weight is collected at follow-up.

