Model 1 specifies only one source of systematic variation among the trial conditions, C_k_. Any factor other than the intervention that favors one condition over the other serves to bias the estimate of the intervention effect. Since this is a randomized trial, there are no differences expected between treatment and control arms in the distribution of covariates. However, there might be unmeasured factors at the various sites that might result in varying effect sizes between the two arms. These factors are potentially confounded with site. In the adjusted analysis, site, interaction between site and treatment, and measured covariates are added to the analysis to reduce confounding and to improve the precision of the estimate of the intervention effect. Covariates can be measured at the site or patient level. Covariates measured at the group (site) level and patient level are distinguished as **G** and **M**. With covariates at two levels and patients nested within sites, we shift to a two-level generalized linear model with logit link. Level 1 involves patient-level variables: $\text{logit}\;\left[Y_{\text{ick}}\right]=\beta_{0c}+\beta_{1c}X_{k}+\beta_{2c}M_{i}+e_{\text{ick}}$, where **M**_i_ is a vector of patient-level covariates (bold indicates a vector throughout this section), *β*_0c,_*β*_1c_, and ***β***_2c_ are patient-level parameters that are allowed to vary over sites, and c = 1, . . ., C clinical sites, and e_ick_ is the residual.

The level-1 model implies three level-2 equations to model variation between sites in patient-level parameters and adds the effect of site-level covariates:

where γ_0._, γ_1_., γ_2_ are parameters to be estimated, Sc is the vector of c-1 site indicators, Gc is the vector of site-level covariates, and u are residual terms. The resulting combined two-level model is of the form:

(1)$$\text{logit}\;\left[Y_{\text{ick}}\right]={ϒ}_{00}+{ϒ}_{01}Sc+{ϒ}_{02}Gc+u_{0c}+\left[{ϒ}_{10},+,{ϒ}_{11},S,c,+,{ϒ}_{12},G,c,+,u_{1c}\right]X_{k}+\left[{ϒ}_{20},+,{ϒ}_{21},S,c,+,{ϒ}_{22},G,c,+,u_{2c}\right]M_{i}+e_{\text{ick}},$$

that simplifies to (Model 2):

(2)$$\text{logit}\left[Y_{\text{ick}}\right]={ϒ}_{00}+{ϒ}_{01}Sc+{ϒ}_{02}Gc+\left[{ϒ}_{10}+u_{1c}\right]X_{k}+{ϒ}_{11}S{\text{cX}}_{k}+{ϒ}_{12}G{\text{cX}}_{k}+\left[{ϒ}_{20}+u_{2c}\right]M_{i}+{ϒ}_{21}ScM_{i}+{ϒ}_{22}GcM_{i}+u_{0c}+e_{\text{ick}},$$

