Abstinence and cost data are used to calculate the incremental net cost per additional quit for AR + IVR participants compared to UC participants. Incremental total costs and cost per participant, by payment source are reported. Incremental cost-effectiveness ratios (ICERs) are measured as: a) incremental intervention costs per incremental quit from health plan/insurer and patient perspectives; b) incremental total costs (intervention plus health care expenditures during follow-up) per incremental quit from health system/insurer and patient perspectives; c) incremental intervention costs per incremental quality-adjusted life-year (QALY) saved from a societal perspective; and d) incremental total costs (intervention plus health-care expenditures during follow-up) per incremental QALY saved from a societal perspective. QALYs for each intervention arm are estimated using life expectancy data and responses from interviewer-administered EQ5D-5L.

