#### *Sensitivity and threshold analyses*

Sensitivity of cost-effectiveness ratios to key parameters: intervention acceptance, intervention costs, abstinence rate, discount rate, pharmacotherapy use and costs, and QALYs saved are measured. Threshold analyses for key parameters are used to identify input levels that alter conclusions. The cost-effectiveness analysis above reflects a deterministic approach using standard univariate and multivariate sensitivity analyses to test the robustness of the results. Based on the results of these analyses, probabilistic sensitivity analyses will be considered, but only if the standard sensitivity tests are unclear or not informative [36-39].

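### Baseline EQ-5D-5L is collected, but no method described for quality of life or QALYs conditions on it; baseline-adjusted regression would be more precise and needs no new data

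*Protocol article*

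**What the plan says.** The Health-related quality of life section (Study measures) has EQ-5D-5L taken "at baseline and six- and twelve-month follow-up for assessing changes in health-related quality of life for AR + IVR versus UC participants". It continues: "Responses are combined with remaining life expectancy data for current and former smokers", in order "to estimate differences in expected quality-adjusted life years saved by treatment group". Under Specific Aim 3 the construction is again at arm level: "QALYs for each intervention arm are estimated using life expectancy data and responses from interviewer-administered EQ5D-5L". These QALYs are the denominators of two of the four planned ratios: (c), which uses intervention costs, and (d), "incremental total costs (intervention plus health-care expenditures during follow-up) per incremental QALY saved from a societal perspective".

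Covariate adjustment is described elsewhere. Under Specific Aim 1, site, its interaction with treatment, and "measured covariates are added to the analysis to reduce confounding and to improve the precision of the estimate of the intervention effect". Specific Aim 4 restates Models 1 and 2 in Poisson form for visits. Specific Aim 3 has no such restatement, and the list under Covariates and effect modifiers does not include baseline EQ-5D. The Other patient information section says that age and other variables "are collected at baseline for primary and secondary outcome analyses"; EQ-5D is not in that list either.

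On uncertainty, the Sensitivity and threshold analyses section says: "The cost-effectiveness analysis above reflects a deterministic approach using standard univariate and multivariate sensitivity analyses to test the robustness of the results". QALYs saved is one of the parameters varied there. Baseline utility is not named.

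**The concern.** The baseline questionnaire is the one measurement likely to predict follow-up utility well, and the trial already pays to collect it. The article suggests two uses of the data: a contrast of changes between arms, and arm-level QALYs built from the responses. Neither uses baseline in the most efficient way.

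- If raw arm-level responses are compared, a chance difference in baseline utility passes into the follow-up difference in proportion to the correlation.
- If change scores are compared, the whole baseline difference is subtracted although only part of it persists, so the error runs the other way.

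What is at stake is the precision of the quality-of-life comparison and of the QALY difference under ratios (c) and (d). There is also the risk of choosing an adjustment after the ratios have been seen. The primary abstinence analysis is not affected.

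**Working it through.** **The article's own figure.** The only design calculation is for abstinence: 864 patients for 15% versus 23%, 2:1, 80% power, two-sided 0.05, no continuity correction (Power section). The pooled-variance formula gives 288 UC + 576 AR + IVR = 864, so it reproduces. This point does not depend on it, and the article states no EQ-5D SD, QALY or ratio to reproduce.

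**Inputs**
- Arm sizes 600 and 300: the Randomization section gives 300:150 at each of two sites.
- Utility SD: assumed 0.20 (range 0.15 to 0.30), the same at each visit.
- Correlation rho between any two visits: assumed 0.5 (range 0.3 to 0.7).
- Complete data. At 85% follow-up every SE rises by 1/√0.85 = 1.08 and the comparison between methods is unchanged.

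**Step 1: size of a chance baseline difference.** k = √(1/600 + 1/300) = 0.0707. SE = 0.20 × 0.0707 = 0.0141. The 95% limit is 1.96 × 0.0141 = 0.028; over SD 0.15 to 0.30 it is 0.021 to 0.042.

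**Step 2: what each method does with a difference of +0.028 (rho 0.5)**
- Follow-up values only: carries rho × 0.028 = +0.014.
- Change score: shifts by (rho − 1) × 0.028 = −0.014.
- Baseline-adjusted regression: removes the part predicted by baseline, so no shift is expected.

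These are shifts given a particular imbalance. Over randomizations all three average zero.

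**Step 3: SE of the 12-month EQ-5D difference**
- Follow-up only: SD × k = 0.0141.
- Change: SD × k × √(2(1 − rho)) = 0.0141.
- Adjusted: SD × k × √(1 − rho²) = 0.0141 × 0.866 = 0.0122.

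The adjusted variance is lower than follow-up only by a factor term rho², and lower than change by (1 − rho)². Both are positive for any rho between 0 and 1.

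**Step 4: SE of a within-trial 12-month QALY difference.** Assume the trapezoid rule, with weights 0.25, 0.5 and 0.25 at 0, 6 and 12 months (sum of squares 0.375).
- Unadjusted variance per patient: 0.04 × [(1 − rho) × 0.375 + rho] = 0.04 × 0.6875 = 0.0275. SE = √0.0275 × 0.0707 = 0.0117.
- Slope of QALY on baseline: 0.25 + 0.75 × rho = 0.625. A baseline difference of 0.028 therefore moves the unadjusted QALY difference by about 0.017 (0.010 to 0.032 over the assumed ranges).
- Adjusted variance: 0.0275 − 0.625² × 0.04 = 0.011875. SE = √0.011875 × 0.0707 = 0.0077.

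**Step 5: SEs over the correlation range (SD 0.20)**

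| rho | 12-month, follow-up only | 12-month, change | 12-month, adjusted | QALY, unadjusted | QALY, adjusted |
|---|---|---|---|---|---|
| 0.3 | 0.0141 | 0.0167 | 0.0135 | 0.0106 | 0.0082 |
| 0.5 | 0.0141 | 0.0141 | 0.0122 | 0.0117 | 0.0077 |
| 0.7 | 0.0141 | 0.0110 | 0.0101 | 0.0127 | 0.0065 |

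All entries scale with the SD: multiply by 0.75 for SD 0.15 and by 1.5 for SD 0.30.

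**The case against.** The strongest reply is that this reads an estimator into silence. The reference to changes stands under Study measures and says why EQ-5D is collected; it does not commit to a change score. The Aim 3 sentence names inputs to the QALY and no model. The article nowhere says that EQ-5D or QALYs will be left unadjusted, and a condensed article may leave a QALY regression to a health-economic plan. That stands: the article fixes no estimator, and a reader who infers a settled unadjusted or change-score analysis goes beyond the text. What remains is that Aims 1 and 4 have covariate models, Aim 3 has none, the covariate list omits baseline EQ-5D, and both uses suggested by the text are less efficient than the alternative.

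A reader might also infer that a baseline imbalance is multiplied over remaining life. With SD 0.25, one SE of imbalance is 0.0177. Over an assumed 15 to 20 years that gives 0.5 × 0.0177 × 15 = 0.13 to 0.7 × 0.0177 × 20 = 0.25 undiscounted QALYs, or 0.08 to 0.11 at correlation 0.3. This supposes that each arm's observed utility is projected over a lifetime. The text is equally compatible with utilities and life-years assigned by smoking status, where the arm difference is driven mainly by quits and the imbalance largely drops out. The documents do not support a lifetime figure.

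The same caution applies to age: the article does not say whether life expectancy is applied by age, so no effect of age imbalance on QALYs can be derived.

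Finally, quality of life is not among the outcomes listed in the abstract and has no hypothesis test of its own, so there is no stated power to lose. For 12-month utility the gain is modest, 13% of the SE at correlation 0.5. An unstable cost per QALY could remain unstable after adjustment.

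**Conclusion.** The point holds as one of efficiency and pre-specification. No method described conditions on baseline utility, and regression on it is more precise than either raw arm-level responses or change scores at every correlation between 0 and 1. At assumed SD 0.20 and correlation 0.5, the SE falls by 13% for the 12-month difference (0.0141 to 0.0122) and by 34% for an unadjusted trapezoid QALY difference (0.0117 to 0.0077). The SD, the correlation, equal variances, complete data and the trapezoid rule are assumptions; the direction of the result does not depend on the particular SD or correlation chosen.

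It is not a finding of bias. Chance imbalance averages zero under randomization, and the two simpler methods err in opposite directions when an imbalance occurs. Nor does it show that the cost-per-QALY result will be distorted over a lifetime, because the projection is not specified.

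**What to change.** Add to the Health-related quality of life section and to Specific Aim 3 that:

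- the six- and twelve-month EQ-5D differences between arms will be estimated by linear regression on arm, baseline utility and site, with age as an optional further covariate decided in advance;
- the within-trial utility or QALY difference that feeds ratios (c) and (d) will be adjusted for the same terms, using patient-level values;
- unadjusted differences and ratios will be shown alongside.

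The existing rule on deaths in the cost-effectiveness analysis need not change. If the full protocol or health-economic plan already specifies this, a confirming sentence is enough.

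The change is to wording only, since baseline EQ-5D, age and site are already recorded. The small downsides are that a missing baseline EQ-5D needs simple imputation of that covariate, and that two versions of each cost-per-QALY ratio are reported.

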#### *Other patient information*

Age, sex, ethnicity, race, height, weight, marital status, educational attainment, annual income, insurance coverage, time after waking before first cigarette, confidence for successful quitting, Patient-Health Questionaire-2 depression screen, and the Audit-C alcohol screen, are collected at baseline for primary and secondary outcome analyses. Weight is collected at follow-up.

### Data analysis

This section describes the methods used to evaluate the specific aims of the I-TSAR study. The primary aim for this study has been harmonized with the other NIH-funded CHART collaborative group studies and approved by the CHART DSMB.

#### *Specific Aim 1: estimate self-reported thirty-day abstinence at six and twelve months for patients assigned to receive inpatient AR + IVR compared to usual care*

Based on KPNW and OHSU member data and meta-analyses of effectiveness of hospital cessation programs with ≥1 month postdischarge follow-up, we expect about 15% of usual care patients and 23% of AR + IVR participants will be abstinent six months following discharge. The primary analysis assumes that nonrespondents are smokers.

The treatment effect on the primary outcome (and other binary outcomes) will be evaluated using logistic regression, logit[Y_ik_] = β_0_ + β_1_X_k_ + e _ik_ (Model 1), where Y_ik_ is the binary indicator of the observed binary smoking status for the i^th^ patient (i = 1,. . .,n_k_) within the k^th^ treatment condition (k = 1,2), X_k_ is the fixed effect of the k^th^ condition, that is, intervention or control, and β_0_, β_1_ are parameters to be estimated. Any difference between the predicted and observed values is left to the residual error (e _ik_) in this model. Multiple regression methods available in SAS PROC Logistic [33] will be used to estimate the parameters of this generalized linear model. The intervention fixed effect will be tested using the score *χ*^2^ test.

Model 1 specifies only one source of systematic variation among the trial conditions, C_k_. Any factor other than the intervention that favors one condition over the other serves to bias the estimate of the intervention effect. Since this is a randomized trial, there are no differences expected between treatment and control arms in the distribution of covariates. However, there might be unmeasured factors at the various sites that might result in varying effect sizes between the two arms. These factors are potentially confounded with site. In the adjusted analysis, site, interaction between site and treatment, and measured covariates are added to the analysis to reduce confounding and to improve the precision of the estimate of the intervention effect. Covariates can be measured at the site or patient level. Covariates measured at the group (site) level and patient level are distinguished as **G** and **M**. With covariates at two levels and patients nested within sites, we shift to a two-level generalized linear model with logit link. Level 1 involves patient-level variables: $\text{logit}\;\left[Y_{\text{ick}}\right]=\beta_{0c}+\beta_{1c}X_{k}+\beta_{2c}M_{i}+e_{\text{ick}}$, where **M**_i_ is a vector of patient-level covariates (bold indicates a vector throughout this section), *β*_0c,_*β*_1c_, and ***β***_2c_ are patient-level parameters that are allowed to vary over sites, and c = 1, . . ., C clinical sites, and e_ick_ is the residual.

The level-1 model implies three level-2 equations to model variation between sites in patient-level parameters and adds the effect of site-level covariates:

where γ_0._, γ_1_., γ_2_ are parameters to be estimated, Sc is the vector of c-1 site indicators, Gc is the vector of site-level covariates, and u are residual terms. The resulting combined two-level model is of the form:

(1)$$\text{logit}\;\left[Y_{\text{ick}}\right]={ϒ}_{00}+{ϒ}_{01}Sc+{ϒ}_{02}Gc+u_{0c}+\left[{ϒ}_{10},+,{ϒ}_{11},S,c,+,{ϒ}_{12},G,c,+,u_{1c}\right]X_{k}+\left[{ϒ}_{20},+,{ϒ}_{21},S,c,+,{ϒ}_{22},G,c,+,u_{2c}\right]M_{i}+e_{\text{ick}},$$

that simplifies to (Model 2):

(2)$$\text{logit}\left[Y_{\text{ick}}\right]={ϒ}_{00}+{ϒ}_{01}Sc+{ϒ}_{02}Gc+\left[{ϒ}_{10}+u_{1c}\right]X_{k}+{ϒ}_{11}S{\text{cX}}_{k}+{ϒ}_{12}G{\text{cX}}_{k}+\left[{ϒ}_{20}+u_{2c}\right]M_{i}+{ϒ}_{21}ScM_{i}+{ϒ}_{22}GcM_{i}+u_{0c}+e_{\text{ick}},$$

where combined effects, for example, **S**cX_k_, indicate an interaction. Not shown here are the multiple slope coefficients on the vectors of **M** and **G** covariates. We will test the assumption of linear relationships between quantitative covariates and the logit of smoking status by adding quadratic terms to Model 2. The test of homogeneity of covariate regression slopes across conditions and sites is the test that the associated parameter (for example, γ_11_) is 0. When the covariates were measured at baseline, this is a test of whether the variable moderates treatment response. This could provide useful information on subgroups of smokers for whom the intervention is more or less effective.

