### Randomization

Randomization is conducted using a selection and documentation procedure that ensures balanced enrollment over time, blinds the TTS to the assignment, and prevents postrandomization assignment changes. Each site randomly assigns 450 patients on a 2:1 ratio (300 AR + IVR: 150 UC) using secure, preprinted, sequentially numbered randomization envelopes. The study statistician developed a randomization algorithm using a predetermined randomization sequence with permuted blocks of randomly varying size. The block size is masked from all except the data coordinating center (DCC) statistician and programmer. This strategy ensures balanced enrollment over time and eliminates the ability of the TTS to guess assignment prior to randomization.

The randomization algorithm matches group assignment to a four-digit randomization number, where the first digit is the site ID (KP = 1; OHSU = 2) and the last three digits are the randomization sequence number. The randomization number is printed on a label and affixed to the outside of each randomization envelope. Inside each envelope are two identical self-adhesive labels printed with the randomization number and treatment arm assignment. The labels are used to confirm and track randomization. The envelopes are placed in a box in ascending order. The treatment arm assignment is not discernable from the outside of the sealed envelope.

Once a patient is prescreened eligible, the TTS selects the next randomization envelope in sequence, along with other patient enrollment forms, and proceeds to the patient’s room. After the eligible patient provides informed consent and completes baseline assessment, the TTS opens the randomization envelope and records the participant’s assignment. At the KP site, the TTS affixes one of the randomization labels to the site’s randomization log, and then records the date and time of randomization, the participant ID number, and the TTS’ initials on the log. A second label is affixed to the enrollment checklist form before transmission to data entry staff. At the OHSU site, the TTS opens the randomization envelope, places one of the randomization labels in the patient’s research chart, records the date and time of randomization, participant ID number, and the TTS’ initials. A second label is affixed to the enrollment checklist before transmission to KP data entry staff.

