#### *Power*

A 2:1 ratio of AR + IVR to UC for 900 randomized participants will provide adequate power to detect an eight percentage point difference in thirty-day point prevalence abstinence at six months (our primary outcome), assuming an unbiased method of assigning an outcome to nonrespondents. The unbalanced design requires 864 participants to achieve 80% power, with two-tailed α set at .05, to detect a difference in thirty-day abstinence of eight percentage points between treatment groups. We expect the UC group will achieve a 15% abstinence rate, based on analyses of EMR data (unpublished) for similar populations at each site. An odds ratio of 1.65 for patients with >30 days of follow-up [3] results in a 23% expected abstinence rate for the AR + IVR group. The power calculations were conservative [25-28] and no continuity correction was applied. Rounding up to 900 total participants added an additional measure of conservatism.

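### The primary test leaves out hospital, although randomization is done within hospital, and the planned adjusted model cannot stand in for it: a valid test with a small, cheap improvement available

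*Protocol article*

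**What the plan says.** **Allocation.** The Randomization section states: "Each site randomly assigns 450 patients on a 2:1 ratio (300 AR + IVR: 150 UC"). It uses permuted blocks and randomization numbers whose first digit is the site. Hospital is therefore a stratification factor in fact, whether or not it is called one.

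**Primary test.** Under Specific Aim 1: "The treatment effect on the primary outcome (and other binary outcomes) will be evaluated using logistic regression". Model 1 has an intercept and a treatment term, and the score chi-square test is attached to that term. The next paragraph confirms this: "Model 1 specifies only one source of systematic variation among the trial conditions".

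**Adjusted analysis.** Model 2 then adds site, the site-by-treatment interaction and measured covariates, with better precision as one stated aim. It also carries random terms for the intercept, the treatment effect and the covariate effects by site. The covariate list (Covariates and effect modifiers) includes the cessation programme used and the medications used. The Aim 4 text refers to Models 1 and 2 together as belonging to the primary aim.

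**Baseline data.** Other patient information lists variables, among them time to first cigarette and confidence in quitting, that "are collected at baseline for primary and secondary outcome analyses". Amount smoked per day is not in that list. It is part of the inpatient consult and appears in the covariate list. Confidence is not in the covariate list.

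**The concern.** When allocation is fixed at 2:1 within each hospital, a difference in abstinence between hospitals cannot contribute to the difference between arms. A pooled chi-square still counts that between-hospital variation as noise. Its variance is then too large, its type I error falls below 5%, and some power is lost. The usual remedy is to analyse by the stratum used for randomization.

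The protocol has no usable version of that analysis. In Model 2 as written:

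- With the site-by-treatment term present, the treatment coefficient is the effect at the reference hospital, not an overall effect.
- Two hospitals that already have a fixed indicator leave nothing from which to estimate random site terms.
- Programme and medication use follow randomization and are what the intervention is meant to change. Adjusting for them would remove part of the effect.

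At stake is a modest amount of power, and clarity about which model decides the trial.

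**Working it through.** **1. The plan's own figure.** Inputs from the Power section: UC 15% ("We expect the UC group will achieve a 15% abstinence rate"), AR + IVR 23% ("results in a 23% expected abstinence rate for the AR + IVR group"), "with two-tailed α set at .05", 80% power, 2:1, no continuity correction.

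Pooled rate = (0.15 + 2×0.23)/3 = 0.2033, and 0.2033×0.7967 = 0.1620.

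n(UC) = [1.96·√(1.5×0.1620) + 0.8416·√(0.15×0.85 + 0.23×0.77/2)]² / 0.08² = [0.966 + 0.391]² / 0.0064 ≈ 287.9, so 288.

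Total 3×288 = 864, which agrees with "The unbalanced design requires 864 participants to achieve 80% power". With 300 v 600 the same method gives 81.7%. The planned power is therefore that of the unadjusted test and does not depend on any adjustment.

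**2. Why the pooled test turns conservative.** With equal-sized sites and no treatment effect, the pooled variance uses p̄(1−p̄). The correct within-site quantity is the mean of p(1−p) over the two sites. The excess is (p₁−p₂)²/4. The true type I error is about P(|Z| > 1.96/√ratio), where ratio = within-site/pooled.

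| Abstinence by site (assumed) | Pooled | Within-site | Ratio | Type I error |
|---|---|---|---|---|
| 15/15% | 0.1275 | 0.1275 | 1 | 5.0% |
| 12.5/17.5% | 0.1275 | 0.1269 | 0.995 | 4.9% |
| 10/20% | 0.1275 | 0.1250 | 0.980 | 4.8% |
| 5/25% | 0.1275 | 0.1175 | 0.922 | 4.1% |

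The error never rises above 5%.

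**3. Power with a common odds ratio of 1.65.** Simulated, 300:150 per site, 400,000 trials per scenario, pooled score test v site-stratified Mantel-Haenszel score test:

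| UC by site (assumed) | Pooled | Stratified | Gain (points) |
|---|---|---|---|
| 15/15% | 77.7% | 77.7% | 0 |
| 12.5/17.5% | 76.9% | 77.2% | 0.3 |
| 10/20% | 75.7% | 76.6% | 0.9 |
| 5/25% | 69.0% | 72.9% | 3.9 |

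The levels start below 80% because odds of 0.15/0.85 × 1.65 give 22.6%, not the planned 23%. Only the last column concerns the site term.

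**4. Power with overall rates held at the planned 15% v 23%.** 200,000 trials per scenario, pooled v stratified, by assumed between-site odds ratio:

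- 1.0: 81.9 v 81.9%
- 1.5: 82.0 v 82.2%
- 2.0: 82.1 v 82.6%
- 3.0: 82.5 v 83.7%

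Gains run from 0 to 1.2 points. Type I error of the pooled test was 4.7 to 5.0%.

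**5. Adding a baseline predictor score.** Same planned rates, 10,000 trials per scenario (Monte Carlo standard error about 0.4 point), unadjusted v adjusted, by assumed AUC:

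- 0.58: 82.0 v 82.7%
- 0.64: 82.3 v 84.0%
- 0.70: 81.7 v 84.8%
- 0.75: 82.2 v 86.9%

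Gains run from 0.7 to 4.7 points. The protocol gives no figure for predictor strength.

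**The case against.** The case for leaving the plan alone is strong in several respects.

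- The unadjusted test is valid and is the test on which the sample size was based. An unadjusted primary test with an adjusted companion analysis is an accepted choice. This stands.
- The Study interventions section gives about 15% abstinence for patients of both hospitals, and the Population section calls the two sites' demographics similar. On those figures the site term gains nothing. This also stands.
- The Discussion expects care to be linked more easily at the HMO than at the academic hospital. A reader might infer that the protocol itself predicts different abstinence by site. It does not: the passage is about integration and access, and gives no site-specific usual-care rates.
- The simulated powers of 69% to 78% might be read as a failure of the 80% plan caused by omitting site. They are not: most of the shortfall comes from the smaller effect simulated in those runs.
- The primary aim is harmonized across the CHART studies and approved by their DSMB, and covariates make the odds ratio conditional. Both points stand, and reporting the crude result alongside meets them.

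The argument that adjustment is already planned does not answer the point, because Model 2 as written gives no overall site-adjusted treatment effect.

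**Conclusion.** Holds as a minor efficiency and consistency point. The trial randomizes within hospital. Its only named primary test ignores hospital, and the adjusted model provided cannot take over that role.

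The stronger reading, that the test is invalid or gives away material power, is not supported. Type I error is not inflated, and 900 patients deliver the stated 80% at 15% v 23%. The site term alone is worth about 0 points on the protocol's figures, roughly 0.3 to 1 point for moderate assumed differences (12.5/17.5% to 10/20%), and near 4 points only at 5/25%. That last case is a between-site odds ratio of (0.25/0.75)/(0.05/0.95) = 6.3, far from anything in the document. Prespecified baseline predictors would bring more, about 1 to 5 points, but only under the assumed AUC range of 0.58 to 0.75.

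**What to change.** Before outcomes by arm are seen, state that the primary test is the treatment term in a main-effects logistic model with a fixed site indicator and no interaction (with site alone, the Mantel-Haenszel score test is equivalent). Preferably add two or three named baseline predictors already collected: time to first cigarette, cigarettes per day and confidence in quitting. Exclude programme and medication use from any model that estimates the treatment effect, and drop the random site terms. Keep the site-by-treatment interaction as a secondary analysis. Use the same model form for the other binary outcomes.

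Report the crude comparison as supporting, so that the result can be set beside the other CHART studies.

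The cost is a change of wording and, since the primary aim is harmonized, agreement with the consortium and its DSMB. No new data are needed. The one drawback is that the adjusted odds ratio is conditional and will not equal the crude one exactly.
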